### Study data

Data collection occurs at baseline, 3 months, and 6 months, and at each time point, the participating parent and their teen will complete an online survey administered using REDCap. The teen will also complete three 24-h dietary recalls using the Waterloo Eating Behavior Questionnaire (WEBQ), and parents will measure their teen’s height and weight following the protocol and tools provided by the research team. Finally, the study team will extract 14 days of Fitbit Flex 2 (Fitbit Inc., San Francisco, CA) wear for each teen at each assessment time point using Fitabase (Small Steps Lab LLC, San Diego, CA, USA), an online platform designed specifically for research using Fitbits. Participants will receive their Fitbit at baseline. *See* Fig. 3 for the SPIRIT Fig [49, 50]. to see when data collection occurs and for a detailed list of data that are collected to address the primary and secondary aims of this study. The complete SPIRIT checklist can be found in Additional files 1 and 2.

**Fig. 3 Fig3:**
[figure not shown]
SPIRIT Figure

### Primary outcomes

#### Change in weight outcomes

Height and weight will be measured by parents using the Centers for Disease Control and Prevention home protocol [51] and will be used to calculate Body Mass Index (BMI) kg/m^2^; this is a valid and reliable method to assess BMI in children [52]. Each participant will be mailed a digital scale (Active Era) and tape measure (HDX) so that all measurements are taken using the same instruments. This procedure has been validated to assess height and weight at home among adolescents and found to provide valid assessment [52]. Teen BMI z-scores will be computed using a Stata macro developed by the World Health Organization, whereby a BMI z-score > 1 and ≤ 2 Standard Deviation = overweight and > 2 Standard Deviation = obese) [53].

Change in physical activity behaviors will be assessed using a Fitbit Flex 2, which can be immersed in water [54] (Fitbit Inc., San Francisco, CA), and with a questionnaire. Each participant will be mailed their Fitbit Flex 2 at baseline. From the Fitbit Flex 2, total steps per day for a period of 14 days will be extracted using the Fitabase platform. The child physical activity questions were modelled after the International Physical Activity and the Environment Network questions [55], and they ask about participation in physical education at school in the past week, involvement in team sports, and number of days of moderate-vigorous physical activity in the previous week.

Change in dietary habits will be measured using the WEBQ, a 24-h dietary recall web-questionnaire developed by the University of Waterloo, which has been validated in children [56], and with a questionnaire. Three 24-h dietary recall WEBQs (including 1 weekend day) will be analyzed using the Food Processor Software (ESHA Research, Salem, OR) using the 2015 Canadian Nutrient data file. An index of diet quality using the Healthy Eating Index adapted for Canadian food recommendations will be computed. The index computes a score from 0 to 100, where ≤ 50 is categorized as poor diet, 50–80 as needing improvement, and ≥ 80 as being good [57, 58]. In addition, seven dietary questions were included in the child’s questionnaire, and these questions were taken from the 2016 Canada Community Health Survey [59], with some questions originating from the Behavioral Risk Factors Surveillance System [60] and Centers for Disease Control and Prevention National Youth Physical Activity and Nutrition Study [61]. Questions asked about previous week and previous day consumption of fruits and vegetables, 100% fruit juices, and sugar-sweetened beverages.

Change in sedentary behaviors will be measured with an adapted version of French et al.’s assessment of screen time which has been found to be sensitive to intervention-mediated change [62]. Two questions ask the amount of time children spend in front of screen in their free time on weekdays and weekend day.

### Secondary outcomes

Adherence will be measure with web-analytic data that is internally collected within the Aim2Be app for children. Adherence will be first operationalized as time spent using Aim2Be, number of days using Aim2Be, and number of tasks completed. Given that web-analytic data tracks all features that children are using and the content utilized, if variability in the data allow it, profiles of users will be used as outcomes.

Mediators that will be examined with respect to adherence are linked to the theoretical framework of Aim2Be (see Fig. 2). The list of mediators are included in Appendix 1 and include 1) an assessment of satisfaction with Aim2Be for gamification mediators; 2) measures of motivation, self-efficacy, and psychological autonomy for behavioral mediators; and 3) assessments of the household environment (family communication and functioning), parenting styles and practices, access/opportunities (cell phone, TV in bedroom, and co-participation in physical activity), modelling healthy behaviors (e.g., parent’s own behaviors), and parental support for environmental mediators.

Moderators that will be examined will be taken from the demographic questions (i.e., age and gender), as well as assessment of enjoyment and preferences for engaging in the behaviors targeted by Aim2Be (five items assessing food and sedentary behaviors preferences and enjoyment for physical activity), knowledge of current health recommendations (eight Yes/No items asking about the physical activity, diet, screen time, and sleep recommendations), weight concerns (two items), self-esteem/optimism (six items) [63], and anxiety/worries (three items) [64].

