Aim2Be was iteratively and incrementally developed. The first version of Aim2Be (v1) was field tested for 4.5 months among 301 teens between 14- and 17-years old and 315 parents. The quantitative evaluation revealed that teens who were moderately and/or highly engaged in the app (> 30 min of app usage) as compared to those with low engagement (≤ 30 min of app usage) significantly increased their motivation and self-efficacy to improve their dietary habits (i.e., limit sugar-sweetened beverages and increase intake of fruits and vegetables) and sedentary behaviors (i.e., limit screen time). At 4.5 months, children significantly increased their previous day’s intake of fruits and vegetables, decreased their consumption of 100% fruit juice, and reduced their screen time. In addition, parents who were more engaged with Aim2Be v1 reported significant improvements in the children’s dietary behaviors (i.e., increased intake of fruits and vegetables and decreased intake of sugar-sweetened beverages). Additionally, multiple rounds of qualitative evaluations were conducted among 36 teens/preteens and 24 parents. The qualitative evaluations included both focus groups and 2-week prototype testing, followed by semi-structured interviews. The results of these evaluations led to numerous improvements in Aim2Be including clarifying the overall purpose of Aim2Be, supplementing the tracking and check-in sections, adding more engaging features, and syncing the app with physical activity monitoring (i.e., Fitbit).

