		3.2 Social support (practical)
		3.3 Social support (emotional)
		6.1 Demonstration of behaviors
		6.2 Social comparison
		13.1 Identification of self as role model
Virtual Coach *PT, T, P*	The Virtual Coach, Aimbot, is a digital bot with a range of pre-programmed prompts, questions, and answers designed to guide users in the app with behavior change in an empathetic way. All app users can access Aimbot. The content is based on queries that arose during the pilot.	3.2 Social support (practical)
Health coach *PT, T, P*	The health coach, trained in motivational interviewing, provides support to app users through an in-app coaching interface in which the Coach and user can have one-on-one messaging conversations to provide more tailored and more personal health behavior guidance.	2.2 Feedback on behavior

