### Study conditions

Intervention condition participants will have access to the full version of the Aim2Be app (as described in Table 1) for 6 months. In addition, participants (teens and parents) will have the option to access a health coach who can support them in health behavior change using motivational interviewing techniques. The health coach has training in motivational interviewing and expertise in lifestyle management and working with families. The health coach will communicate with participants through the in-app text feature, and participants have the option to schedule a live text session if they wish to do so. The health coach will send an initial contact to all participants and will send follow-up supportive messages. The exact messaging and frequency of messaging that the health coach will provide to participants cannot be predicted, as this coaching will be individually tailored to the questions and concerns participants raise with the health coach, and the frequency with which they reach out to the health coach. This is in line with the autonomy support model featured throughout Aim2Be, where participants can choose the health behaviors on which they wish to focus.

Waitlist control condition participants will be put on a waitlist for 3 months during which time they receive a brochure with Canadian health recommendations about physical activity, diet, screen time, and sleep habits (this represents the duration in which they are part of the efficacy trial—see Fig. 1). Once their 3-month assessment is complete, they will have access to Aim2Be app, with no health coach, for the following 3 months. Participants will have access to all features of the Aim2Be app except the health coach and will be assessed 3 months after they were given access to the Aim2App with no health coach. This 3-month period will be compared to the 3-month period of the intervention condition to determine differences in adherence in Aim2Be with and without health coach support.

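### As defined, time and days in Aim2Be include use of the in-app health coach, which only one arm has, so two of the three adherence outcomes partly measure the coaching itself

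*Protocol article*

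**What the plan says.** All places are in the protocol article.

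- **Outcome.** Secondary outcomes gives the source: "Adherence will be measure with web-analytic data that is internally collected within the Aim2Be app for children". It then names three measures: "Adherence will be first operationalized as time spent using Aim2Be, number of days using Aim2Be, and number of tasks completed". Statistical analyses repeats them as time in the app, days in the app and tasks completed, each with its own linear regression after transformation. None is ranked first.
- **Scope of the logs.** "Given that web-analytic data tracks all features that children are using and the content utilized", user profiles may also serve as outcomes if the data vary enough. No feature is set aside for time or days.
- **Where coaching happens.** Study conditions: "The health coach will communicate with participants through the in-app text feature, and participants have the option to schedule a live text session". The coach makes a first contact with everyone in that arm and then sends follow-up messages. The Health coach row of Table 1 lists the coach as a feature for preteens, teens and parents that "provides support to app users through an in-app coaching interface in which the Coach and user can have one-on-one messaging conversations".
- **Comparator.** From month 3 to month 6 the waitlist arm has every part of the app other than the coach. Those three months are set against three months of the intervention arm to judge what coaching does to adherence.

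**The concern.** Secondary aim 1 asks whether adding coaching to the Aim2Be programme increases adherence. If minutes with the coach count as time using Aim2Be, one arm can score on something that the other arm does not have. A difference in time or days would then mix two things: contact with the coach, which is the treatment being tested, and greater use of the aims, tasks and content that both arms share. A reader of the results could not separate them from total time or total days.

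The comparison is not marginal to the design. The Sample size calculation asks for at least 80 families per condition for BMI z-score and moves to 100 per group because of the adherence comparison. That comparison is sized with a one-sided test, and any added coach time pushes in the direction that favours coaching.

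**Working it through.** **Step 1. The three outcomes against the feature that differs between arms.**

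| Outcome | Can use of the coach add to it directly? | Open to the waitlist arm? |
|---|---|---|
| Time using Aim2Be | Yes, each minute in the coach interface | No |
| Days using Aim2Be | Only on days when the app is opened solely for the coach | No |
| Tasks completed | No, reading or answering a message completes no task | Not applicable |

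That coach minutes count as time is an inference from four statements taken together: the outcome is time in the app, coaching is in the app, the logs cover all features, and no exclusion is given. The article does not state it outright.

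**Step 2. The plan's own figure.** The article gives 77 per group for a 20% difference with one-sided alpha .05 and 80% power. A two-proportion formula with pooled variance gives 77 for 40% against 60% (odds ratio 2.25). The pairs matching the stated odds ratio of 2.33 (30% against 50%, or 50% against 70%) give 74. For enrolment, 77/(0.85 × 0.92) = 98.5 and 77/(1 − 0.23) = 100, so 100 per group reproduces. None of this bears on the outcome definition; 77 is used below only as the group size.

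**Step 3. What added coach time would do to the time outcome.** Assume log-normal time, identical use of shared features in both arms, and coach messaging that raises total time by a fraction f throughout the coach arm. The standardised difference is d = ln(1 + f)/σ, where σ is the log-scale SD. The chance that a one-sided .05 test favours coaching is Φ(d·√(n/2) − 1.645), with n = 77 and √(77/2) = 6.205.

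For f = 0.20 and σ = 1.0: d = 0.182, and Φ(0.182 × 6.205 − 1.645) = Φ(−0.51) = 0.30.

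| f | d (σ = 1.0) | One-sided .05 (nominal 5%) | Two-sided .05, upper side (nominal 2.5%) |
|---|---|---|---|
| 10% | 0.095 | 15% | 9% |
| 20% | 0.182 | 30% | 20% |
| 30% | 0.262 | 49% | 37% |
| 50% | 0.405 | 81% | 71% |

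For f = 20%, the one-sided figure runs from 41% at σ = 0.8 to 19% at σ = 1.5. For scale, 77 per group has 80% power one-sided for d = (1.645 + 0.842) × √(2/77) = 0.40.

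**Step 4. Only part of the arm messages the coach.** A simulation used 77 per group, log-SD 1, half the coach arm messaging, a fixed number of added minutes for those who do, and 4,000 trials per cell. The one-sided rates of an apparent benefit were:

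| Median time in app | 5 min added | 10 min added | 20 min added |
|---|---|---|---|
| 30 min | 16% | 33% | 65% |
| 60 min | 10% | 18% | 34% |
| 120 min | 8% | 9% | 17% |

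Every input in Steps 3 and 4 other than n and alpha is assumed; the article gives no median, SD, uptake or messaging time. The tables show that the answer depends on those inputs. They do not estimate the bias in this trial. No figure is given for days, because nothing indicates how often a child would open the app only for the coach.

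**The case against.** Five points can be made for the plan.

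1. **Logging rules may sit elsewhere.** What counts as a session or an active day is often left to a fuller document, and the article says only that adherence is operationalised this way first. This stands as a limit on certainty. But the article does fix the outcome, twice, as total use of the app, and as fixed it includes the coach.
2. **Using the coach may be adherence.** Table 1 lists the coach among the app's features, and the aim speaks of adherence to the intervention. Total use is a defensible target on that reading, which is why it should still be reported. For time and days, though, the comparison then becomes partly circular.
3. **Tasks completed is a built-in check.** This stands. A reader might infer that any positive adherence result could mean only that children opened coach messages. The document does not support that: tasks completed has its own regression and is not directly inflated. The possible user profiles are a weaker safeguard, being conditional and leaving the three regressions unchanged.
4. **Coach time may be small or may displace other use.** Live sessions are optional, and the article says that message frequency cannot be predicted. Parents have a separate app whose use is not counted, and the virtual coach is open to everyone. This also stands: the addition need not be pure, and it need not be large.
5. **The aim is secondary and called exploratory.** True, and the primary efficacy comparison is untouched.

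**Conclusion.** The point holds in a limited form. Followed as written, time and days in the child app include use of a feature that only one arm has, so a difference in either partly reflects the exposure itself. This rests on the inference that coach messaging is logged as app use.

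Two stronger readings are not supported. One is that adherence is certain to rise with coaching whatever children do elsewhere in the app. The article gives no uptake or messaging time, coach use may replace other use, and one of the three outcomes is not directly affected. The other is to size the problem from the version 1 field test, which compared more engaged teens with "those with low engagement (≤ 30 min of app usage)". That split comes from 14- to 17-year-olds followed for 4.5 months, whereas this trial analyses transformed continuous outcomes over three months, so no such line is crossed.

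The size is therefore unknown. Under the assumptions in the working it runs from negligible (8% against a nominal 5%) to serious (65%). The remedy is cheap enough to be worth making without knowing which applies.

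**What to change.** For the secondary aim 1 comparison:

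- Define time and days on features available to both arms, leaving out the coach interface. The Social Wall stays in: the coach moderates it, but both arms have it.
- State a rule for sessions that mix coach messaging with other use. A day should count when any shared feature is used, so that a child whom a coach message brings back to the programme is still credited.
- Report coach-interface time and days separately for the intervention arm, and total use alongside, so that displacement can be seen.
- Do not base a claim that coaching raises adherence on total time or total days alone when shared-feature use and tasks completed do not agree with it.

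No new data collection should be needed, since the article says that the logs track all the features children use. The cost is one definition, a session-splitting rule that will be somewhat arbitrary, and some extra log processing. The definition should be fixed before the logs are compared by arm.

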### Statistical analyses

To address the primary aims, multilevel mixed-effect linear and logistic models, which account for the repeated nature of the data, will be used to test whether zBMI, dietary quality, fruit and vegetable intake, sugar-sweetened beverage intake, physical activity, and screen time at 3 months differ between Aim2Be and control condition participants. To address the secondary aim that examines whether health coaching influences adherence to the Aim2Be intervention, linear regressions will be used to compare the time spent using Aim2Be, number of days using Aim2Be, and number of tasks completed. Three analyses will be run, one for each adherence variables (i.e., time spent in app, numbers of days in app, and tasks completed). As the data are expected to be skewed, the dependent variables will be log-transformed or optimal transformation will be used to deal with the skewness of the data. Finally, examination of the mediators and moderators of adherence will use path analyses and relevant socio-demographic covariates and explore whether recruitment routes influenced adherence (e.g., self-referral or healthcare facility referral). Multiple imputation techniques will be used to deal with the missing data. Analyses will be conducted in Stata (StataCorp LLC, College Station, TX, USA) and MPlus (Muthen & Muthen, Los Angeles, CA, USA).

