### Study aims and hypotheses

The primary aim of this RCT is to test the efficacy of Aim2Be with health coaching at improving weight outcomes and lifestyle behaviors among 10- to 17-year-old children compared to those randomized into a waitlist control condition. Children whose families receive the Aim2Be with health coaching are hypothesized to significantly decrease their age adjusted zBMI scores as well as significantly increase their moderate-vigorous physical activity, improve dietary behaviors (i.e., increase fruit and vegetable intake, improve dietary quality, and reduce sugar-sweetened beverage intake), and reduce screen time.

The secondary aims of the RCT are to 1) test whether supplementing the Aim2Be program with health coaching increases adherence to the intervention and 2) examine the mediators and moderators of adherence to the Aim2Be intervention. Given the exploratory nature of these aims, no hypotheses are stated.

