### Sample size calculation

Based on previously published data [31], the RCT will have 80% power at an alpha of .05 to detect a .5 decrease in BMI z-score when the sample size in each group is 60. The BMI z-score was used to calculate sample size because this is the most difficult variable to change and requires the largest sample size of all of the primary outcomes. Based on this and accounting for both missing data and attrition, we project needing at least 80 families in each condition. However, to be able to detect a 20% difference in adherence (e.g., secondary aims outcome) between the two intervention groups (odds ratio of 2.33) at an alpha of .05 with 80% power using a one-sided t-test, 77 families are needed in each group. As the waitlist control group will receive the intervention at 3 months, we require 100 participants enrolled in each group (this accounts for 15% attrition from baseline to 3-month and the approximately 8% of families who will not download the Aim2Be app). Power calculations were conducted in nQuery (Statsols, USA). Based on these computations, we aim to enroll 200 participants in the RCT.

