## Discussion

Although in-person family-based interventions are the standard for supporting families of children with overweight or obesity, these programs are costly and may not reach all those who can benefits from such programs. In addition, these programs often do not meet the needs of many families [12–16]. Therefore, mHealth interventions may provide a viable alternative to in-person family-based interventions; however, the efficacy of such interventions have not been evaluated robustly in the current literature. Evidence from the current RCT will strengthen the current mHealth literature. This RCT will examine the efficacy of Aim2Be in decreasing zBMI scores and improving lifestyle behavior factors. Beyond this, the RCT will examine whether Aim2Be can provide a practical and accessible intervention that improves adherence to lifestyle interventions.

One limitation to the study is the short intervention period, which may not allow for sufficient time to observe changes in the BMI z-score, particularly in an adolescent population. However, the co-primary outcome data on lifestyle behavior (physical activity and diet quality) may provide greater insight into the overall efficacy of Aim2Be. Furthermore, the mediators of behavior change and predictors of adherence will provide insights as to whether the intervention worked as intended. As the trial has a number of inclusion and exclusion criteria, we will gain a better understanding of who is reached by these mHealth lifestyle interventions in these criteria and for whom it appeals to the most. Gaining a better understanding of the mediators and moderators that are linked with intervention adherence will serve to advance the understanding of how mHealth interventions work.

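### Six outcomes hold primary status while only zBMI is sized, at an undivided 0.05: under an any-one-counts reading, the chance of some false-positive primary result is about 23–27%

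*Protocol article*

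**What the plan says.** All references are to the protocol article.

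- **Statistical analyses.** The models for the primary aims ask whether zBMI, three dietary outcomes (overall quality, fruit and vegetables, sugary drinks), "physical activity, and screen time at 3 months differ between Aim2Be and control condition participants". That is six outcomes, with no order among them.
- **Primary outcomes.** Weight, activity, diet and sedentary behaviour all stand under this heading. Adherence is what opens Secondary outcomes.
- **Sample size calculation.** zBMI was chosen for sizing because "this is the most difficult variable to change and requires the largest sample size of all of the primary outcomes". The trial is said to have "80% power at an alpha of .05 to detect a .5 decrease in BMI z-score when the sample size in each group is 60". No other primary outcome is given an alpha or a power.
- **Discussion.** After noting that the period may be too short for zBMI to change, the article adds that "the co-primary outcome data on lifestyle behavior (physical activity and diet quality) may provide greater insight into the overall efficacy of Aim2Be". Only two behaviours are named here, against five in Statistical analyses.
- **Study aims and hypotheses.** Children are expected to "significantly increase their moderate-vigorous physical activity, improve dietary behaviors" and reduce screen time, besides lowering zBMI. The activity hypothesis concerns moderate-vigorous activity. The Primary outcomes section extracts daily Fitbit steps and separately asks for days of moderate-vigorous activity. Statistical analyses says only physical activity.

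**The concern.** The article decides which outcomes are primary, and it chooses six. It does not say how six results combine into one conclusion on efficacy, and its own statements pull in different directions. Sizing on zBMI at the full 0.05 fits a trial with one primary outcome. The plural in the sample size section and the list in Statistical analyses fit six. The Discussion remark leans towards letting a behavioural result speak for efficacy when zBMI does not move.

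At stake is the main claim. With a null zBMI and one behaviour at p < 0.05, the text would let the trial be reported as positive on a primary outcome, and a reader could not tell how easily chance alone produces that. The measured variable is also open: activity and diet each have two instruments, so the number of possible tests is not fixed at six.

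**Working it through.** **Inputs from the article**
- Six primary comparisons at 3 months (Statistical analyses).
- zBMI: alpha .05, power 80%, difference 0.5, 60 per group (Sample size calculation). Neither the SD nor the sidedness is stated.
- 100 enrolled per group with 15% attrition by 3 months, so 100 × 0.85 = 85 evaluable per group.

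**Assumptions**
- Each outcome is tested two-sided at 0.05. Statistical analyses gives no per-test alpha. The inference comes from the sample size section, where zBMI gets .05 and is compared with the other primary outcomes as if all faced the same level.
- A common correlation of 0 to 0.4 between test statistics. The article gives none.

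**Step 1: the plan's own figure.** n per group = 2·SD²·(z₀.₉₇₅ + z₀.₈₀)² / 0.5². Without an SD, 60 cannot be reproduced independently. Solving backwards, SD = 0.5 / [(1.960 + 0.842) × √(2/60)] = 0.978 two-sided, or 1.10 one-sided. An SD of 0.97 gives 60 and an SD of 1.0 gives 63. So 60 is consistent with a two-sided test that spends the whole 0.05 on zBMI.

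**Step 2: any one outcome counts.** With independence, 1 − 0.95⁶ = 0.265. Counting only errors in favour of Aim2Be, 1 − 0.975⁶ = 0.141. For correlated outcomes, 1,000,000 draws of six equicorrelated normal statistics with a threshold of 1.96 give:

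| Correlation | Any false positive (nominal 5%) | False benefit only (nominal 2.5%) |
|---|---|---|
| 0 | 26.5% | 14.1% |
| 0.2 | 25.3% | 12.9% |
| 0.4 | 22.6% | 11.3% |

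**Step 3: all six must succeed.** The chance that all six reject under the null cannot exceed that of one test, so there is no inflation. Joint power cannot exceed the power for zBMI alone. At 60 per group, 80% is then a ceiling and not the power for trial success.

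**Step 4: six primaries kept with alpha split.** 0.05 / 6 = 0.0083, and 1 − (1 − 0.0083)⁶ = 4.9%. With the back-solved SD of 0.978:
- At 60 per group, power for zBMI is Φ(2.802 − 2.638) = 56%.
- At 85 per group, it is Φ(3.335 − 2.638) = 76%.
- 80% power needs 93 evaluable per group.

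With an assumed SD of 1.0 these become 54%, 73% and 97. This is the strictest level that zBMI could face under Holm.

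**Step 5: which reading fits the sample size section.** Step 3 makes 80% a ceiling and Step 4 lowers it. Only a single primary outcome, zBMI, leaves the stated power intact.

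**The case against.** The strongest reply is that this is a condensed article. Multiplicity rules and variable derivation usually belong in an analysis plan, and that plan is not at hand. This stands as far as it goes: the absence of an adjustment method here is not in itself an error. It does not cover the status of the outcomes, which the article fixes, or the sizing on an undivided alpha. A later adjustment across six primaries would change the stated power for zBMI.

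A second reply is that co-primary often means that all must succeed, and the hypotheses are joined by conjunctions. That reading is possible, and it carries no inflation. The article never states it, and the Discussion remark points the other way.

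Several stronger readings are tempting but not supported:
- *That each outcome is stated to be tested at 0.05.* It is not; this is an inference.
- *That 23–27% is the chance of a false claim of efficacy.* It counts errors in either direction. For false benefit with two-sided tests the range is 11–14%.
- *That the Discussion says a behavioural result can replace zBMI.* It says only that such data may add insight, in a remark about limitations.
- *That any positive result would probably come from the least reliable measures.* Diet and screen time are self-reported by unblinded children, but steps are recorded by a device, and zBMI rests on measurements by unblinded parents. This is in any case a question of bias, separate from multiplicity.
- *That the second instruments raise the count to a definite eight, nine or ten tests.* The article does not say that they are tested separately, and the two screen-time items may be parts of one measure.

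**Conclusion.** The point holds in conditional form. The article labels six outcomes primary, sizes one of them on the full 0.05, and does not reconcile the two. If each is tested at 0.05 and any one suffices, the chance of at least one false-positive primary result is about 23–27% against 5%, and of a false benefit about 11–14% against 2.5%. Both ranges assume correlations of 0.4 to 0. If all six are required, the error rate is safe, but the 80% does not describe the chance of trial success. The outcome lists also differ: the Discussion names two behaviours and Statistical analyses tests five, and activity means moderate-vigorous activity in the hypotheses but includes step counts in the measures. Because the trial's central claim depends on which reading applies, this should be settled before any unblinded analysis.

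**What to change.** - Name zBMI at 3 months as the single primary outcome, tested at 0.05. This keeps the sample size statement valid with no change in enrolment.
- Make the five behavioural outcomes secondary, with one named measure each. Test them with Holm at 5%, and allow confirmatory claims only if zBMI is significant. That gate holds the error across all six at 5%. If zBMI is not significant, report the behaviours as supportive.
- Align the named activity measure with the hypothesis: either name a measure of moderate-vigorous activity, or keep steps and reword the hypothesis.
- Bring Study aims and hypotheses, Statistical analyses and the Discussion to the same list and the same terms.
- Recruitment began in January 2019, so this is a substantive change. Record it in the registry entry as a dated amendment, made before unblinded analysis.

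The cost is stricter thresholds and a lower status for the behavioural outcomes, which matters to a team that doubts zBMI can move in so short a period. If six primaries are kept under Holm or Bonferroni instead, zBMI does not keep the full 0.05 and its power must be restated. At the Bonferroni level of 0.0083 it is about 56% at 60 per group and 76% at 85, on a back-solved SD of 0.98 that the article does not state. If all six must succeed, say so and give the joint power.
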